### Study procedure and participant timeline

Potential participants will be screened by telephone to determine eligibility. They will be provided trial information and invited for clinical assessment (either face to face, or via Zoom, during lockdown due to the COVID-19 pandemic). Consent obtained by study physician. At clinical screening, the participant will complete questionnaires, and be assessed against inclusion and exclusion criteria for participation. The study knee will be the one with clinical and radiographic OA, meeting eligibility criteria. Where both knees are symptomatic, the radiographically less severe knee will be used. Where the radiographic severity is the same, the knee with the higher level of pain will be used. The study scheduled assessments and measures are presented in Table 1. At the 4 participant contacts, safety and drug efficacy will be assessed. Participant receipt of study drug will be confirmed within 3 days of prescription.

Throughout the study period, all other usual therapy will be allowed, with the exception of medications that may interact with study medication.

#### Quality assurance

Study personnel will be trained according to the study protocol. They will execute the study using the study’s standard operating protocol book, detailing the procedures to be used, study contacts, measures. Participant assessments will be collected in pre-specified case report forms.

Pill count at the end of the study period will be used to assess compliance with study medication. Participants will be reimbursed for parking and transport costs: they will not be paid to participate in the trial.

### Outcome measures

#### Primary outcome

Change in knee pain between baseline and 12 weeks will be assessed using the Western Ontario and McMaster Universities Osteoarthritis Index (WOMAC) pain scale, a self-administered questionnaire using VAS [27, 28]. Each of the 5 pain scale items will be assessed on a 100 mm VAS. Results will be summed and normalised to a 0–100 scale. Incomplete items will be addressed as recommended in the users guide: where one item is missing, the remainder will be averaged and divided by 5 then normalised. When more than one item is missing, the data will be deemed invalid [28].

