### Sample size

#### Primary outcome

Based on published data, in OA, pain on the WOMAC pain scale (0-100 mm) has a standard deviation (SD) of ≈20 mm [40]. The minimal clinically important difference is 10 mm, with an expectation that 1 in 2 will experience substantial pain relief [41].

This outcome will be analysed using analysis of covariance (ANCOVA) of change in WOMAC pain adjusting for baseline pain. With 64 participants in each arm we will have 80% power to detect a 10 mm difference in change in pain between the intervention and control groups (alpha error 0.05, 2-sided significance at 12 weeks), conservatively assuming a pre-post correlation of zero. With positive correlation the power will be greater than 80%. Based on a conservative 20% loss to follow up we will recruit 160 participants (80 in each arm of the study).

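### The one-missing-item rule for the primary WOMAC pain score conflicts with the complete-form rule and, read literally, makes the score 5 or 25 times too low

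*Protocol article*

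**What the plan says.** The rule is in the protocol article, Methods, Outcome measures, Primary outcome. For a complete form: "Each of the 5 pain scale items will be assessed on a 100 mm VAS", and "Results will be summed and normalised to a 0–100 scale". For a form with one unanswered item: "where one item is missing, the remainder will be averaged and divided by 5 then normalised". For anything worse: "When more than one item is missing, the data will be deemed invalid". The disputed clause therefore applies only when exactly one of the five items is missing. The article attributes the handling of incomplete items to the instrument's users guide. No other section restates or corrects the rule.

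The Sample size section gives the scale on which an error matters: "pain on the WOMAC pain scale (0-100 mm) has a standard deviation (SD) of ≈20 mm", "The minimal clinically important difference is 10 mm", and "With 64 participants in each arm we will have 80% power to detect a 10 mm difference in change in pain".

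**The concern.** Two rules in one paragraph produce the same variable, and they do not agree. A sum of five items needs a division by 5 to reach 0–100; an average of four items does not. The clause for incomplete forms applies the division to the average, so it puts the value on a 0–20 scale and then names a further step without saying what that step does to such a value.

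This is the scoring of the primary endpoint. A form scored this way would enter the analysis as a valid observation on the wrong scale. The multiple imputation planned under Statistical analysis would not catch it, because the score would be present, not missing. At week 12 an affected form would look like a large pain response.

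**Working it through.** **Inputs.** From Outcome measures, Primary outcome: five items, each 0–100 mm; score range 0–100. From Sample size, Primary outcome: SD 20 mm, target difference 10 mm, 64 per arm, 80% power, two-sided alpha 0.05. Assumed, because the documents do not give them: a true score of 50 mm and the number of forms with one missing item.

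**The plan's own figure.** The standardised difference is 10/20 = 0.5. A two-sample t-test needs 63.8, so 64 per arm, and power at 64 is 80.1%. Allowing for 20% loss, 64/0.8 = 80 per arm, 160 in total. The sample size reproduces and is not in question.

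**Complete form, all items 50.** Sum = 250; 250/5 = 50.

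**One item missing, the other four averaging M = 50.** A coherent rule returns M: (4 × 50 + 50)/5 = 50. The written clause can be read in four ways:

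| Reading of the clause | Arithmetic | Score | Error |
|---|---|---|---|
| Average divided by 5, no further change | 50/5 | 10 | 5 times too low |
| Average divided by 5, then the complete-form step (divide by 5) | 50/5/5 | 2 | 25 times too low |
| Average divided by 5, then the 0–20 value stretched to 0–100 | (50/5) × 5 | 50 | none |
| Loose reading: sum of the four items divided once by 5 | 200/5 | 40 | 20% too low |

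The first two follow the words as printed. The third makes the division pointless. The fourth ignores the averaging.

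**Effect on one participant at week 12.** With a complete baseline of 50 and no true change, the recorded change is 10 − 50 = −40 mm or 2 − 50 = −48 mm. The error scales with the score: at a true 30 mm the first reading gives 30/5 = 6, an error of 24 mm.

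**Effect on an arm mean (assumed counts, week 12 only, one arm of 64, true score 50).** Shift = k/64 × error.

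| Affected forms k | Error 40 mm | Error 48 mm |
|---|---|---|
| 1 | 0.6 mm | 0.8 mm |
| 3 | 1.9 mm | 2.3 mm |
| 6 | 3.8 mm | 4.5 mm |

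**Effect on power (assumed rate of 5% in both arms, first reading, true mean 50).** Affected forms have mean 10 and SD 20/5 = 4. Variance = 0.95 × 400 + 0.05 × 16 + 0.05 × 0.95 × 40² = 380 + 0.8 + 76 = 456.8, so SD 21.4 mm. The 10 mm difference is diluted to 0.95 × 10 + 0.05 × 2 = 9.6 mm. The standardised difference is 9.6/21.4 = 0.45, and power at 64 per arm is about 71%. The same calculation gives about 76% at a 2% rate and 63% at 10%. These show sensitivity only.

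**Effect at baseline.** The primary analysis regresses change on treatment and baseline pain. With baseline in the model, the treatment coefficient is the same whether the outcome is change or the week-12 score. A mis-scored baseline is therefore an error in a covariate, not a 40 mm error in the outcome.

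**The case against.** The strongest reply is that the clause does not stop at the division. It ends with a normalising step, and the preceding text uses that word for bringing a score to 0–100. If a 0–20 value is brought to 0–100, the result is correct and the division is merely redundant. The phrase may also be a slip for multiplying by 5, or a poor paraphrase of a sound rule in the users guide, which is not available here. Nothing shows that any form has been scored literally.

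This stands to the extent that one cannot say every participant with a missing item gets a score at least five times too low. A reader might infer that from the division alone, but it holds in only two of the four readings. It does not rescue the text. For a complete form the same step turns a 0–500 sum into 0–100, so it divides; the harmless reading needs it to multiply, in order to cancel the instruction just given. If the phrase is a slip, the sentence is wrong and needs correcting. Nor is this detail left to a fuller document: the article states the rule, and states it badly.

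Two further objections also stand. A reader might infer that a missing baseline item produces a false worsening of tens of millimetres in the treatment comparison. The adjustment for baseline prevents that, and baseline missingness precedes treatment, so randomisation balances it in expectation. A reader might also infer bias between arms or a known loss of power. The documents give no rate of single missing items and no reason to expect it to differ by arm in a double-blind trial with an active placebo.

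**Conclusion.** The concern holds in this form: the clause for one missing item is inconsistent with the complete-form rule in the same paragraph. Read literally it turns a score of 50 into 10 or 2, and it is harmless only if the last step undoes the division. For an affected week-12 form from an unchanged participant at 50 mm, the false fall is 40 to 48 mm, four to nearly five times the 10 mm target difference. At baseline the main consequence is a weaker covariate.

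The size per form rests on the assumed score of 50 mm and on the literal readings. The size for the trial is unknown, because it depends on how many forms lack exactly one item and on how the program scores them. The arm-mean and power figures are illustrations, not estimates. The planned sample size is unaffected. A primary-endpoint sentence that can return 2, 10, 40 or 50 for the same form should be corrected before analysis.

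**What to change.** Replace the clause with: *where one item is missing, the mean of the four completed items replaces the missing item, and the five values are then summed and normalised to 0–100 as for a complete form (equivalently, the score is the mean of the four completed items).* The rule for more than one missing item can stay as it is.

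Then check that the scoring program does this, for example with a test form whose four answered items are all 50, which must return 50. If any form was scored with the division by 5, at baseline or week 12, re-score it from the item values. The cost is one sentence, one program check and, only if needed, re-scoring of the affected forms. No new data, change of sample size or change of analysis model is required.

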#### Secondary outcomes

Change in knee symptomatology between baseline and 12 weeks will be assessed using *change in total WOMAC* score (5 pain items, 2 stiffness items and 17 function items, each measured on a 100 mm VAS will be added and the results normalised to 1–100). A measure of knee overall function is recommended by OARSI.

*Pain severity, achieving a clinically significant response* assessed by percentage reduction in participant’s current level of knee pain, recorded on VAS, ranging from no pain to the worst pain imaginable (0 – 100 mm), from baseline to 12 weeks. The proportion attaining a substantial response (designated ≥ 50% reduction in pain intensity) and a moderate response (designated as a ≥ 30% reduction in pain intensity, as defined by the International Pain Society [24, 25].

### Other measures

#### Measures of knee pain

*Pain severity* (Numerical Rating Scale, NRS) will be assessed at each participant contact, including telephone contacts (0, 2, 6, 12 weeks) using a categorised numerical rating scale (0–10). (How would you rate your pain on a 0–10 scale at the present time? 0 is no pain, 10 is pain as bad as it could be). This will be used for an area under the curve analysis, and not for assessment of change between 0 and 12 weeks.

*Pain diagram:* participants will indicate body areas where they feel pain at 0 and 12 weeks.

*Pain Detect* questionnaire will be applied at 0 and 12 weeks. (0–35). Scores of > 12 indicate increased odds of central pain sensitisation in OA [29].

#### Measures of functional status and disease severity

*ACR functional class rating* [30] *will be assessed*) at baseline and 12 weeks using Likert scale 0–4.

*Investigator assessed global assessment* of OA (Likert scale, 0–4) at baseline and 12 weeks.

*General health status* at 0 and 12 weeks, quality adjusted life years (QALYS) will be derived from the generic preference based, validated Assessment of Quality of Life 8D (AQol-8D) measure [31, 32].

*Muscle strength,* predominantly of quadriceps and hip flexors, measured by dynamometry at both legs simultaneously at baseline and 12 weeks [33].

*Severity of radiographic knee OA:* Osteophytes and joint space narrowing will be graded from a standing semi-flexed AP radiograph of the study knee using the Altman atlas (0–3, [34]). We have high reproducibility for grading at the knee (Kappa statistic 0.93, [35]).

#### Other measures of response

*Pain acceptability,* over the past 48 h at baseline and 12 weeks. (Thinking only of the pain you felt in your knee during the last 48 h, if you were to remain with that pain for the rest of your life would that be acceptable to you?)

*Patient’s global impression of change scale*, measured on Likert scale, 0–7 at 2, 6 and 12 weeks. (Since joining the study, would you describe the change (if any) in activity, limitations, symptoms, emotions and overall quality of life, related to your painful condition (knee pain)?)

#### Other measures

*Demographic and anthropomorphic measures*: Age, gender, height, weight, smoking, medical conditions, highest education level, current employment and current medications will be measured at baseline.

*Tampa Scale of Kinesiophobia (TSK) Scale (17 item)* will be used to assess fear of movement/(re) injury, at 0 and 12 weeks.

*International physical activity questionnaire (IPAQ)-SF* [36] at 0 and 12 weeks will assess physical activity.

*Pittsburgh sleep quality index* (PSQI) [37], administered at 0 and 12 weeks to assess sleep quality and disturbance.

*Hospital Anxiety and Depression Scale* [38]: Mood symptom severity (anxiety and depression subscales) will be assessed at 0 and 12 weeks.

#### Treatment and safety issues

*Analgesic use* will be documented at 0 and 12 weeks.

*Treatment guessing* at 12 weeks participants will be asked to guess whether they were on active study drug, placebo or whether they were not sure.

*Participant rating of study drug and side effects* on a likert scale, ranging from excellent to unacceptable.

*Adherence and compliance:* Participants will return unused study drug at the final visit. Capsules will be counted to assess adherence.

### Safety monitoring

*The UKU Side Effects Rating Scale* [39], a standardised, physician-administered interview for assessing the severity and impact of side effects of psychotropic drugs on daily function will be used to assess for adverse effects. In addition, participants will be asked to contact research staff in the event of any adverse events. Any serious adverse events and their relationship to study medication will be recorded and reported to the Ethics Committees. Participants’ physicians will be informed of their patient’s involvement in the study.

*Adverse events* will be recorded where present, by participant report on their occurrence and actively elicited at each contact. Should adverse events occur, participants will be followed until these have resolved.

### Dissemination policy

Trial results, regardless of statistical significance, will be presented in the peer reviewed literature after the final participant completes the study period. All authors will be required to contribute to and approve the submitted manuscripts, as per the Vancouver authorship guidelines. Upon publication of the primary manuscript, participants will be provided with the results, and informed of their group allocation.

### Sample size

#### Primary outcome

Based on published data, in OA, pain on the WOMAC pain scale (0-100 mm) has a standard deviation (SD) of ≈20 mm [40]. The minimal clinically important difference is 10 mm, with an expectation that 1 in 2 will experience substantial pain relief [41].

This outcome will be analysed using analysis of covariance (ANCOVA) of change in WOMAC pain adjusting for baseline pain. With 64 participants in each arm we will have 80% power to detect a 10 mm difference in change in pain between the intervention and control groups (alpha error 0.05, 2-sided significance at 12 weeks), conservatively assuming a pre-post correlation of zero. With positive correlation the power will be greater than 80%. Based on a conservative 20% loss to follow up we will recruit 160 participants (80 in each arm of the study).

#### Secondary outcomes

The detectable differences of secondary outcomes that will be able to be detected with an alpha error of 0.05, 2-sided significance and 80% power are as follows:
*Difference in WOMAC total* of 10 mm, normalised 0-100 mm, with a SD of 20 mm.*Difference in proportion of participants achieving a 30 and 50% reduction in pain (VAS) at 12 weeks of 21.7%* based on the published placebo response in pooled results from 2 clinical trials of duloxetine in knee OA of 44.9 and 30.9% respectively [42].

### Statistical analysis

Summary statistics comparing randomised arms at baseline will be tabulated. Intention to treat analyses of primary and secondary continuous outcomes will be performed by linear regression adjusting for the baseline of the outcome variable where relevant. The proportion achieving each of ≥ 30 and ≥ 50% reduction in pain, representing “moderate improvement” and “substantial improvement” will be examined using log-binomial regression to estimate risk ratios and confidence intervals directly, as will other binary outcomes. Ordinal outcomes will use proportional odds regression models, with assessment of the proportionality. If the proportion of missing data in an outcome is greater than 5% then multiple imputation will be used. Supplementary analyses will be performed adjusting for imbalanced baseline factors prognostic of outcome. The total quantum of pain for each subject will use the area under the curve of the NRS over 0, 2, 6 and 12 weeks, with analysis performed using linear regression.

***Prespecified sub group analyses*** will be performed according to gender, median age, the painDETECT score > 12 or < =12 (central pain sensitisation), TSK scale > 37 or ≤ 37 (fear avoidance), PSQI > 5 vs PSQI ≤ 5 (sleep quality), HADS-A ≥ 8 vs < 8 (Anxiety), HADS-D ≥ 8 vs < 8 (Depression), HADS-A or HADS-D ≥ 8 or < 8 8 (Mood disorder), in those with and without previous injury, previous knee surgery, and according to radiographic grade of osteoarthritis (define categories/grades). Analyses will use regression models with interaction terms for intervention with each subgroup factor.

No adjustment will be made for multiple testing and statistical significance will be set as a two-sided *p* value < 0.05.

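### The area under the curve of NRS pain is analysed by linear regression with no baseline covariate named, which leaves precision unused

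*Protocol article*

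**What the plan says.** The Statistical analysis section of the protocol article gives the NRS summary its own sentence: the total pain of each participant is the "area under the curve of the NRS over 0, 2, 6 and 12 weeks, with analysis performed using linear regression". No covariate appears there.

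Earlier in the same paragraph is the rule on baseline adjustment: analyses of "primary and secondary continuous outcomes will be performed by linear regression adjusting for the baseline of the outcome variable where relevant". A later sentence adds: "Supplementary analyses will be performed adjusting for imbalanced baseline factors prognostic of outcome".

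The NRS is neither a primary nor a secondary outcome. It appears under Other measures, Measures of knee pain, where its role is fixed: "This will be used for an area under the curve analysis, and not for assessment of change between 0 and 12 weeks". Table 1 schedules it at baseline and at weeks 2, 6 and 12. The other pain-severity scale, the 100 mm VAS, and the WOMAC are scheduled only at baseline and week 12.

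For the primary outcome, the Sample size section specifies "analysis of covariance (ANCOVA) of change in WOMAC pain adjusting for baseline pain" and notes that a positive pre-post correlation would raise power above the planned level.

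**The concern.** The adjustment rule does not clearly reach this analysis. It names primary and secondary outcomes, and it adjusts for the baseline of the outcome variable. An area under the curve has no baseline value of its own, and the week 0 score is already one of its components. An analyst following the text could reasonably regress the area on treatment alone.

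That would have two costs. Variation between participants that existed before treatment stays in the residual and widens the confidence interval. A chance difference between arms in baseline pain also passes into the estimated effect. This matters somewhat because the area under the curve is the only use the article states for the week 2 and week 6 pain scores, so it is the trial's one view of pain over the course of treatment.

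**Working it through.** **The plan's own figure.** The article states: "With 64 participants in each arm we will have 80% power to detect a 10 mm difference in change in pain", with an SD of about 20 mm and two-sided alpha of 0.05. The normal approximation gives n = 2 × (1.960 + 0.842)² × 20² / 10² = 62.8, so 63 per arm. The t-test version gives 63.8, so 64 per arm, with power of 80.1%. Allowing for 20% loss, 64 / 0.8 = 80 per arm, or 160 in total. The plan's figures reproduce. The article gives no power for the NRS area under the curve, so no stated figure is contradicted here.

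**Weights.** With visits at 0, 2, 6 and 12 weeks, the trapezoid rule divided by 12 weeks gives weights of 1/12, 3/12, 5/12 and 3/12. Week 0 therefore contributes 8.3% of the time-averaged score.

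**Variances.** Assume equal SDs at all visits (in SD units) and an equal correlation r between any two visits. The sum of squared weights is (1 + 9 + 25 + 9)/144 = 0.3056.

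- Variance of the averaged score: V = r + (1 − r) × 0.3056
- Covariance with baseline: c = 1/12 + (11/12) × r
- Residual variance after adjusting for baseline, as a fraction of unadjusted: 1 − c²/V
- Power of the unadjusted test at the effect for which the adjusted test has 80%: Φ(2.80 × √(1 − c²/V) − 1.96)

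| r (assumed) | V | c | Variance ratio | Reduction | Extra patients needed if unadjusted | Unadjusted power when adjusted is 80% |
|---|---|---|---|---|---|---|
| 0.3 | 0.514 | 0.358 | 0.75 | 25% | 33% | 68% |
| 0.5 | 0.653 | 0.542 | 0.55 | 45% | 82% | 55% |
| 0.7 | 0.792 | 0.725 | 0.34 | 66% | 198% | 37% |

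At r = 0 the reduction is only about 2%. If follow-up visits correlate at 0.7 with each other but baseline correlates less with them, the ratio is 0.82 at a baseline correlation of 0.3 and 0.62 at 0.5. The gain is then smaller but still present.

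**Carry-over of baseline imbalance.** The expected shift in the unadjusted mean difference is c times the baseline difference. With an assumed NRS SD of 2 and 64 per arm, the standard error of a baseline difference is 2 × √(2/64) = 0.354 points. A one-standard-error imbalance shifts the result by 0.358 × 0.354 = 0.13 points (r = 0.3), 0.542 × 0.354 = 0.19 (r = 0.5) or 0.725 × 0.354 = 0.26 (r = 0.7). Of each, only 0.083 × 0.354 = 0.03 comes from having week 0 inside the area. The rest comes from the correlation of baseline with later scores.

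**Validity.** In 20,000 simulated trials per value of r, with no treatment effect and 64 per arm, the unadjusted test rejected in 4.8% to 5.1% of trials. Among the trials whose baseline difference exceeded 1.96 standard errors, it rejected in about 16%, 28% and 46% (r = 0.3, 0.5, 0.7), against about 4% to 7% with adjustment.

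**The case against.** The strongest reply is that the covariate for an exploratory measure is a detail an article may leave to the statistical analysis plan, which is not shown here. The article never says the comparison will be unadjusted, it uses the same regression method as the other continuous outcomes, and its sample size section shows awareness that baseline correlation adds power. A generous reader could take week 0 as the baseline of the NRS and apply the general rule. The supplementary analyses for imbalanced prognostic factors could also pick up a baseline difference.

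Part of this stands. The defect lies in what the article states, and the analysis plan may already supply the covariate. But the article does state a model for this measure, next to a rule worded so as not to cover it. The supplementary route depends on the observed imbalance and is not the main analysis.

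Several stronger readings are tempting and are not supported:

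- A reader might infer that the unadjusted test is invalid. It is not: the raised rejection rates apply only to the roughly 5% of trials with extreme baseline imbalance, and the overall rate stays near 5%.
- A reader might infer that putting week 0 in the area is the main fault. Its weight is 1/12, and dropping it would leave most of the carry-over in place.
- A reader might picture a full 1-point baseline difference. At an SD of 2 and 64 per arm that is 1/0.354 = 2.8 standard errors, a rare event.

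The entry criterion of VAS pain above 30 mm may also narrow baseline spread and weaken the correlation, which would reduce the gain.

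**Conclusion.** The point holds as a modest one about precision. As stated in the article, the NRS area under the curve has no baseline covariate, and the paragraph's adjustment rule does not clearly extend to it. Adjusting would reduce residual variance by about 25% to 66% for between-visit correlations of 0.3 to 0.7. It would also remove a shift of about 0.13 to 0.26 points per standard error of baseline imbalance.

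The correlations, their equality across visits and the NRS SD of 2 are assumptions; the documents give none of them. The measure is neither primary nor secondary, and the primary analysis already adjusts for baseline pain, so the trial's main conclusion does not depend on this.

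**What to change.** State that the area under the curve of the NRS from 0 to 12 weeks will be compared between arms by linear regression adjusting for baseline NRS. Week 0 can stay in the area or be left out; naming the covariate is what recovers the precision.

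The cost is one phrase in the analysis plan and one degree of freedom. Baseline NRS is already scheduled in Table 1, so no new data are needed. The wording should be settled before the allocation code is revealed.

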### Eligibility criteria

#### Inclusion criteria

Male and female participants with painful knee OA (pain for ≥ 3 months), defined according to ACR clinical and radiographic criteria, with pain of > 30 mm on a 100 mm visual analogue scale (VAS) and age 40–75 years required.

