Amitriptyline, another older tricyclic antidepressant, has been used to treat neuropathic pain and fibromyalgia [46, 47]. The recent related Cochrane reviews have suggested that although in unselected patients, overall, these do not show efficacy, the proportion of patients showing improvement is higher in the treated group [46, 47]. However, most of these studies did not use an active placebo, and were thus more likely to have been subject to unblinding, as the anticholinergic effects occur at low dose. The authors concluded that although there was not a clinically significant effect in the whole population, a small, but significant proportion of patients do benefit. However further trials were unlikely to be performed. It is not clear which patients are more likely to benefit. We will examine whether the proportion benefiting is higher in those on active treatment, and attempt to identify which are more likely to benefit based on subgroups identified using simple clinical tools (eg severity of pain, radiographic change, painDETECT for pain sensitisation, Pittsburgh sleep quality index for sleep quality, HADS for mood disorders, etc).

This current trial has a number of strengths. It will be the first to examine whether knee pain in OA is effectively treated by low dose amitriptyline, considered by some to be the gold standard for pain sensitisation [17]. It examines low dose amitriptyline against benztropine, an active placebo, reducing the potential for unblinding. It will explore the role of phenotyping, according to relevant clinical features, using simple clinical tools that may be completed by patients and thus could translate into clinical practice. A potential limitation will be that it may be underpowered to perform subgroup analyses.

This study will provide high level evidence regarding the effectiveness of low dose amitriptyline for knee pain in OA compared to benztropine, in reducing pain and improving function. The examination and identification of subgroups more likely to respond, have the potential of informing future research to optimize pain management in knee OA.

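### Treatment-effect modification by painDETECT, TSK, PSQI, HADS and age is tested only through two-level cut-offs, which costs power if the effect changes gradually with the score

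*Protocol article*

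**What the plan says.** The prespecified subgroup paragraph under Statistical analysis in the protocol article defines each scored modifier by one threshold: "the painDETECT score > 12 or < =12 (central pain sensitisation), TSK scale > 37 or ≤ 37 (fear avoidance"), followed by "PSQI > 5 vs PSQI ≤ 5 (sleep quality), HADS-A ≥ 8 vs < 8 (Anxiety), HADS-D ≥ 8 vs < 8 (Depression"). A combined mood factor is built from the same two HADS thresholds. The subgroup analyses "will be performed according to gender, median age", so age is divided at whatever median the enrolled sample has.

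The test is also stated: "Analyses will use regression models with interaction terms for intervention with each subgroup factor". The split variable is therefore the tested term. The article nowhere names an interaction with a score on its original scale.

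Under Measures of knee pain, painDETECT runs from 0 to 35 and its threshold has a cited basis: "Scores of > 12 indicate increased odds of central pain sensitisation in OA". The article gives no reason for the other thresholds or for the median-age split. The Discussion presents the search for patients more likely to benefit as something the trial will attempt, and concedes: "A potential limitation will be that it may be underpowered to perform subgroup analyses".

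**The concern.** The trial's rationale is that amitriptyline acts on pain sensitisation, and painDETECT is its questionnaire marker for that mechanism. Splitting at 12 treats a score of 13 like 35 and a score of 12 like 0. If benefit rises gradually with the score, the split discards the differences within each half and weakens the interaction test. The same applies to TSK, PSQI, the two HADS subscales and age. The median-age threshold also depends on who enrols, so another trial cannot reproduce it directly.

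What is at stake is the secondary question of who responds. The article already expects these tests to be weak, so an avoidable loss of power makes a real graded relation easier to miss.

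**Working it through.** **Inputs from the article.** Sample size, Primary outcome: WOMAC pain "has a standard deviation (SD) of ≈20 mm", a 10 mm difference, two-sided 0.05, pre-post correlation taken as zero, 64 analysed per arm, 20% loss, 160 recruited. Inclusion criteria: "age 40–75 years required".

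**Assumptions not in the article.** The shape of each score's distribution, the share of participants above each cut-off, and the form and size of the interaction.

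**Step 1: the plan's own figure.** The standard error of the treatment difference is 20 × √(2/64) = 3.54 mm. Then 10/3.54 = 2.83, and power = Φ(2.83 − 1.96) = 0.81 (0.80 with the t distribution). Allowing for loss, 64/0.8 = 80 per arm, 160 in all. The stated figures reproduce. The article gives no power for the interaction tests.

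**Step 2: information kept by a split.** For a treatment effect linear in the score, the share of information kept is the squared correlation between the score and its two-level version. For a normal score with a share p above the cut-off, this equals φ(z)²/[p(1 − p)], where z is the normal quantile at 1 − p. At p = 0.5 it is 0.399²/0.25 = 0.637.

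**Step 3: power.** With 1:1 allocation and 128 analysed, the standard error of the interaction per SD of the score is 2 × 20/√128 = 3.54 mm. For an interaction of b mm per SD, power is Φ(b/3.54 − 1.96) with the continuous score and Φ(√(share kept) × b/3.54 − 1.96) with the split.

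| Modifier as analysed | Information kept | 128 analysed are worth | Power, 10 mm per SD | Power, 5 mm per SD |
|---|---|---|---|---|
| Continuous | 1 | 128 | 81% | 29% |
| Split, 50% above | 0.637 | 81 | 62% | 20% |
| Split, 30% above | 0.576 | 74 | 57% | 19% |
| Split, 20% above | 0.490 | 63 | 51% | 17% |
| Split, 10% above | 0.342 | 44 | 38% | 13% |

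A simulation of 4,000 trials per setting at 10 mm per SD gave slightly lower values in the same order: 78% continuous, and 59%, 53% and 46% with 50%, 30% and 20% above the cut-off. Type I error was about 5% for both forms.

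**Step 4: other distributions, still with a linear effect.**
- A uniform or symmetric two-peaked score split at its median loses about 25%.
- Age truncated to 40–75 (assumed mean 60–65, SD 7–12 before truncation) loses about 30–34% at its median.
- Skewed scores (gamma or exponential, 10–50% above the cut-off) lose about 35–52%.

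**Step 5: the effect steps exactly at the cut-off.** The ranking reverses. Where the split has 80% power, the linear term has 61%, 57% and 50% with 50%, 30% and 20% above. In simulation, a 15 mm step with 30% above gave 46% for the split and 29% for the linear term.

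**Step 6: how weak the tests are.** With a 50/50 split, the standard error of the difference between two subgroup effects is 3.54/√0.25 = 7.07 mm. A 10 mm difference between subgroup effects then has power Φ(10/7.07 − 1.96) = 29%. With a 20/80 split it is 20%.

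**The case against.** The strongest reply is that linearity is an assumption the article does not make. It speaks of sensitisation as present in some patients, and cites a prevalence of about 30% in more severe disease. If sensitisation is present or absent and 12 separates the two well, the split is the better test. A reader might infer from the painDETECT threshold sentence that the marker must be graded, but increased odds above a threshold fit an imperfect two-class marker equally well. This stands, and it is why the cut-off results should stay in the report.

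A reader might also conclude that dichotomising always discards a third or more of the information. The article does not support that: it gives no score distributions and no shares above the cut-offs, and under plausible shapes the loss can be about 25%.

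The 10 mm per SD case is large. It means effects 20 mm apart between patients one SD below and one SD above the mean, twice the difference the trial is sized for. At 5 mm per SD neither test is adequate. So the change improves efficiency but does not cure low power.

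The cut-offs suit the wish for tools usable in practice, they are prespecified, and they are tested by interaction terms rather than by separate within-subgroup tests. Finding responders is not among the aims under Hypothesis and objectives, and the power limit is admitted. It would therefore go too far to say that the trial will wrongly report that painDETECT does not predict response.

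Finally, an analysis plan not shown could add a continuous analysis. That does not remove the point: the article names the tested term, and it is the split variable.

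**Conclusion.** The point holds as a conditional efficiency loss in exploratory analyses. If modification is roughly linear, the split costs about 36% of the information for a near-normal score cut at its median and more at uneven cuts. It costs about 25–34% at the median for uniform scores or truncated age. At 128 analysed and SD 20 mm, a median split lowers interaction power from about 80% to 62% at 10 mm per SD and from about 29% to 20% at 5 mm per SD. If the effect steps at the cut-off, the stated form is the better one.

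These figures rest on assumed distributions and an assumed form of interaction. The primary analysis, the secondary analyses and the sample size are untouched. The change is still worth making, because it costs little and serves a question the trial says it will address.

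**What to change.** In the subgroup paragraph, prespecify for painDETECT, TSK, PSQI, HADS-A, HADS-D and age that the main modifier test is the interaction of treatment with the continuous baseline score. Include the score's main effect and a simple check of linearity, such as a spline or quadratic term. Keep the stated cut-offs to present treatment effects within subgroups, labelled exploratory. Test age as a continuous variable instead of through the median split. Factors that are two-level by nature, such as gender and previous surgery, need no change.

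This is a wording change that needs no new data or participants, and it should be made before the allocation code is revealed. Its costs are less power if the effect truly steps at the cut-off, a linearity assumption, and possible influence of extreme values in skewed scores such as HADS with about 128 analysed. Each marker will also be reported in two forms with no multiplicity adjustment, so the text should state in advance that the continuous test is the main one.
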